## Abstract

**Introduction:**

High-quality bowel preparation is a crucial prerequisite for ensuring the effectiveness of colonoscopy. Although polyethylene glycol (PEG) remains the first-line cleansing regimen recommended by clinical guidelines, its practical application still faces challenges in achieving adequate bowel preparation rates. Transcutaneous electrical acupoint stimulation (TEAS) shows promise in enhancing intestinal motility through gut-brain-microbiota modulation. However, its role in the field of intestinal cleansing remains unclear.

**Methods and analysis:**

This randomized controlled trial will enroll 404 patients undergoing elective colonoscopy. The participants will be randomly allocated to either the TEAS group or the sham-TEAS group, in a 1:1 ratio. TEAS was applied to stimulate the *Zusanli* (ST36) and *Neiguan* (PC6) acupoints using a clinically validated stimulation mode, administered concomitantly with PEG in a combined treatment protocol. The primary outcome measure was the rate of adequate bowel preparation, evaluated with the Boston Bowel Preparation Scale (BBPS). Secondary endpoints encompass colonoscope insertion and withdrawal times, cecal intubation rate (CIR), adenoma detection rate (ADR), first defecation time, total defecation frequency, final stool characteristics, adverse event incidence, and satisfaction.

**Discussion:**

By bridging traditional acupoint therapy with quantifiable neurogastroenterological outcomes, this study aims to establish TEAS as a scalable adjunct in bowel preparation protocols.

**Trial registration:**

International Traditional Medicine Clinical Trial Registry, ITMCTR2025001121. Registered on April 30, 2025, http://itmctr.ccebtcm.org.cn/.

## Introduction

Colorectal cancer (CRC) is the most commonly diagnosed gastrointestinal (GI) cancer, representing 1.8 million cases and 881,000 deaths globally, and constituting one in 10 cancer cases and deaths (1). Epidemiological data indicate a strong positive correlation between CRC incidence and increasing levels of economic development (2). Advanced adenomas are the most well-known precursor lesions of colorectal carcinoma (3). The early identification and resection of these lesions through screening programs have been associated with a reduction in CRC incidence and mortality rates (4, 5). A variety of screening methodologies are currently accessible, broadly categorized into stool-based tests, such as the guaiac-based fecal occult blood test and fecal immunochemical test, and direct visualization techniques, including sigmoidoscopy and colonoscopy (6, 7). Colonoscopy is used both as a primary screening tool and a confirmatory diagnostic procedure following a positive result from non-invasive tests. When comparing the performance of a single screening round, endoscopic techniques generally yielded higher detection rates of advanced neoplasia than one-time stool-based blood tests (8–10).

High-quality bowel preparation is a critical determinant of polyp and early-stage tumor detection rates during colonoscopy (11). Inadequate bowel cleansing has been associated with missed lesions, prolonged procedure duration, and a potential increase in complication rates (12–15). Current guidelines consistently recommend polyethylene glycol (PEG) as the first-line bowel preparation agent, which achieves reliable cleansing through an osmotic laxative mechanism (16). However, PEG regimens still exhibit clinical limitations, most notably suboptimal bowel cleansing efficacy. Data indicate that patients receiving conventional protocols continue to have a relatively high incidence of residual bowel content, with adequate bowel preparation rates (Boston Bowel Preparation Scale, BBPS ≥6/Ottawa Bowel Preparation Quality Scale, OBPQS ≤7) ranging from 53.1–82.2% using standardized scoring systems (17–21). Various strategies have been explored to address this challenge, including modified PEG regimens (e.g., low-volume split-dose administration), combination with prokinetic agents, or adjunctive use of stimulant laxatives like sodium picosulfate (22–25). However, these methods remain suboptimal due to variable cleansing efficacy, risks of electrolyte disturbances, and potential drug interactions. Consequently, developing non-pharmacological strategies to enhance bowel cleansing efficacy, mitigate laxative-induced gastrointestinal adverse effects, and improve treatment adherence represents a critical research direction in optimizing bowel preparation protocols.

Transcutaneous electrical acupoint stimulation (TEAS), a non-invasive stimulation therapy that combines the advantages of acupuncture and transcutaneous electrical nerve stimulation, has emerged as a promising therapeutic approach in clinical practice (26). As suggested by previous studies, TEAS has been shown to promote recovery of bowel function through modulation of the brain-gut axis (27–30). Recent clinical studies further demonstrate its therapeutic effects in functional gastrointestinal disorders (e.g., functional dyspepsia and chronic constipation), showing significant symptom relief and motility enhancement, potentially mediated by peripheral nerve activity regulation (30, 31). Additional study has confirmed that by enhancing parasympathetic activity, TEAS facilitates high-amplitude propagated contractions, which are critically required for efficient colonic propulsion (32). These mechanisms provide potential scientific support for TEAS in optimizing bowel preparation quality and alleviating the discomfort associated with the bowel preparation process.

To address the critical gap in evidence regarding TEAS for bowel preparation, we conducted a randomized, placebo-controlled clinical trial. This study hypothesizes that TEAS could optimize the quality of bowel preparation and alleviates bowel preparation-related symptoms, offering a potential adjunct to standard pharmacological regimens.

## Methods and analysis

### Trial design

This trial is designed as a randomised, controlled, single-blinded single-center superiority trial with a primary endpoint of the rate of adequate bowel preparation measured by the BBPS score (33). The study will be conducted at Zhejiang Provincial Hospital of Traditional Chinese Medicine in China. A total of 404 participants will be randomly allocated to either the TEAS group (Group T, *n* = 202) or the sham-TEAS group (Group S, *n* = 202) in a 1:1 ratio. To ensure objective and accurate evaluation, all study-related endoscopic procedures were performed by senior endoscopists. The research protocol adheres to the Standard Protocol Items: Recommendations for Interventional Trials (SPIRIT) guidelines (34). Table 1 presents a succinct timeline detailing the study visits, enrolment process, interventions, and assessments performed on participants. The flowchart is illustrated in Figure 1.

**Table 1 tab1:** Standard protocol items: recommendations for interventional trials (SPIRIT) schedule for enrollment, interventions, and assessments.

	Study period					
	Enrolment	Allocation	Post-allocation			Close-out
Timepoint	−24 h	0	1 h	3 h	6 h	24 h
Enrolment						
Eligibility screen	×					
Informed consent	×					
Allocation		×				
Interventions						
Sham-TEAS group			×			
TEAS group			×			
Assessments						
Baseline variables	×	×				
Quality of bowel preparation (BBPS)				×		
Rate of adequate bowel preparation				×		
Colonoscope insertion time				×		
Colonoscope withdrawal time				×		
Cecal intubation rate (CIR)				×		
Adenoma detection rate (ADR)				×		
First defecation time						
Total defecation frequency						
Final stool characteristics						
Adverse reaction profiles						
Satisfaction metrics						

**Figure 1 fig1:**
[figure not shown]
Consolidated standards of reporting trials (CONSORT) diagram for this trail.

### Eligibility criteria

#### Inclusion criteria

Patients eligible for the trial must comply with all of the following at randomization:

Individuals aged 18–80 years, undergoing colonoscopy for any indication, irrespective of gender;Participating in the study voluntarily and signing written informed consent.

#### Exclusion criteria

Severe cardiovascular and respiratory ailments, liver and kidney dysfunction, cancer, or other serious organic diseases;Administered pharmacological agents that affect gastrointestinal motility within the preceding 2 weeks;History of digestive system surgery (except appendectomy and cholecystectomy);Gravida, puerperant and patients with positive urine pregnancy tests;Allergy to skin preparation or electrodes;Familiarity with acupoints.

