### Randomization and blinding

This single-blinded trial implemented CONSORT-compliant randomization and blinding protocols (36), and subjects were assigned to the TEAS group and the sham-TEAS group in a 1:1 ratio. To ensure assessment objectivity, screening and outcome assessors remained blinded to treatment allocation status throughout the study period. All recordings were deidentified by removing all patient identifiers and temporal markers to eliminate assessment bias. The TEAS-administering acupuncturists maintained awareness of treatment allocation while remaining blinded to study outcomes. A computer-generated block randomization system with concealed allocation utilized numbered, sealed envelopes containing group assignments, secured by ward nurses until post-allocation unblinding. Primary endpoints were evaluated by two gastroenterologists independently conducted blinded assessments by reviewing endoscopic videos. A standardized operational protocol (fixed electrode stimulation duration) was implemented for double-blind control, while enabling dynamic adjustment of stimulation intensity based on individual tolerance thresholds. A blinding assessment will be conducted after colonoscopy completion and before unblinding, using a standardized questionnaire asking patients: “Which treatment do you think you received? (A. Active TEAS; B. Sham TEAS; C. Uncertain).” The success of blinding will be quantified by calculating the Bang Blinding Index.

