#### TEAS and sham-TEAS

TEAS Protocol: The TEAS intervention protocol employed an acupoint combination targeting *Neiguan* (PC6) and *Zusanli* (ST36) (see Figure 2 for anatomical landmarks). PC6 acupoint is located on the anterior forearm, 2 cun proximal to the transverse wrist crease, between the tendons of the palmaris longus and flexor carpi radialis muscles. ST36 acupoint is situated on the anterolateral aspect of the leg, 3 cun inferior to the lower border of the patella, one finger-breadth lateral to the anterior crest of the tibia. Pre-intervention anatomical validation by acupuncturists (<3 mm positioning tolerance). The stimulation system comprised hydrogel self-adhesive electrodes (diameter: 20 mm) interfaced with a transcutaneous acupoint electrical stimulator (SNM-FDCM01, Ningbo Maida Medical Instrument Company, Ningbo, China). The intervention period overlapped with the PEG administration period and lasted 1 h from the first dose of PEG ingestion (Figure 3). The stimulation parameters were set as follows: a train on-time of 2 s and off-time of 3 s, pulse width of 0.5 ms, pulse frequency of 25 Hz, and amplitude of 2–10 mA (at the maximum level tolerated by the subject).

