**Figure 3 fig3:**
[figure not shown]
The administration of TEAS treatment protocol.

Sham-TEAS Protocol: Sham acupoint stimulation was performed using the same devices to provide identical parameters as TEAS, with sham points positioned outside the anatomical course of relevant meridians: the sham-point of PC6 is approximately 15 cm up to the elbow joint and lateral to the real PC6 acupoint and the sham-point of ST36 is approximately 10 cm down to the knee and lateral to the real ST36 acupoint. The temporal schedule and ancillary procedures (electrode placement duration, PEG coordination) mirrored the intervention group.

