#### Rationale for parameter selection

PC6 (Neiguan) and ST36 (Zusanli) are classic acupoints for gastrointestinal disorders. ST36 is the Lower He-Sea point of the stomach, and PC6 connects to the Yin Link Vessel. Modern studies confirm that PC6 electroacupuncture promotes gastric emptying and small intestinal transit via vagal afferent activation (38) and reduces postoperative nausea and vomiting (39). ST36 stimulation promotes distal colonic peristalsis and accelerates colonic transit through the sacral parasympathetic efferent pathway (40). Although abdominal surface stimulation may be more directly relevant to promoting bowel motility (41), it was not adopted due to potential provocation of PEG-related abdominal pain, low evidence level, and unclear optimal parameters. In contrast, limb-based PC6 and ST36 are easy to secure and do not interfere with bowel preparation. Regarding stimulation parameters (42, 43): 25 Hz is a mid-frequency dense-disperse wave that effectively activates vagal efferent fibers to promote colonic motility. A pulse width of 0.5 ms is standard for transcutaneous electrical nerve stimulation, balancing skin penetration depth and fiber selectivity. The 1-h duration overlaps the critical period of intestinal filling and enhanced peristalsis following PEG ingestion. Intensity is individualized to patient tolerance from 2 to 10 mA, ensuring efficacy without causing pain or skin injury.

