### Safety assessment

All enrolled patients were included in the safety assessment. Safety outcomes encompassed predefined adverse events (including ear skin rash, dizziness, palpitation, and intolerable diarrhea requiring intervention) during treatment and follow-up phases. All safety-related data were meticulously documented for safety findings.

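### Current is set by felt tolerance in both arms, but no exclusion covers reduced sensation or broken skin at the electrode sites

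*Protocol article*

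**What the plan says.** **Intensity.** In the protocol article, TEAS and sham-TEAS, active stimulation lasts one hour at an "amplitude of 2–10 mA (at the maximum level tolerated by the subject"). The sham paragraph of that section states: "Sham acupoint stimulation was performed using the same devices to provide identical parameters as TEAS". The sham points are moved away from the active ones, but sham patients still receive current.

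**Stated protection.** Rationale for parameter selection says: "Intensity is individualized to patient tolerance from 2 to 10 mA, ensuring efficacy without causing pain or skin injury". Randomization and blinding describes the procedure as "enabling dynamic adjustment of stimulation intensity based on individual tolerance thresholds".

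**Who may enter.** Inclusion criteria admit "Individuals aged 18–80 years, undergoing colonoscopy for any indication, irrespective of gender", subject to consent. Exclusion criteria has six items. One concerns the electrodes, "Allergy to skin preparation or electrodes", and one concerns general health: "Severe cardiovascular and respiratory ailments, liver and kidney dysfunction, cancer, or other serious organic diseases". The other four cover recent drugs acting on gut motility, digestive surgery, pregnancy and the puerperium, and knowledge of acupoints.

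**Monitoring.** Safety assessment gives examples of predefined events: a rash at the ear, then "dizziness, palpitation, and intolerable diarrhea requiring intervention".

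**The concern.** The article makes the patient's own perception the control on intensity and says that this control prevents injury. That works only if the patient can feel the stimulus normally where the electrodes sit. The exclusion list deals with electrode risk but stops at allergy, so it does not remove patients in whom the control is unreliable. It does not remove patients whose skin at a site is already damaged either.

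At stake is an avoidable exposure, in both arms because sham delivers the same current. A lesser consequence concerns dose. In a patient with reduced sensation the setting may drift towards the 10 mA limit for want of a signal, so the stated link between tolerance and effective intensity does not hold for that patient.

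**Working it through.** The core of this point is a comparison of sections. Arithmetic enters only for scale and for the cost of the fix.

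**1. Reliance on tolerance against the eligibility list**

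| Patient | Does felt tolerance protect, as the rationale says? | Is the patient excluded as written? |
|---|---|---|
| Normal sensation, intact skin | Yes, on the article's reasoning | No, and need not be |
| Reduced sensation at a forearm or leg site | Not reliably: the signal that sets the limit is impaired | Only if the cause counts as a serious organic disease |
| Broken or infected skin at a site, normal sensation | Tolerance still gives a signal, but skin at the site is already damaged | No |
| Implanted electronic device | The article does not say; its tolerance argument concerns pain and skin injury | Only if the underlying disease is severe |

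The second row is the direct gap in the plan's own reasoning. The third row is a tension with the aim of avoiding skin injury; it is not a failure of the tolerance rule. The fourth row cannot be settled from the article.

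**2. Is the gap closed elsewhere?** Standardization of intervention implementation covers operator training in point location, electrode placement and settings, with retraining and audit. It describes no check of the patient's sensation or skin. Recruitment limits the trial to supervised inpatients but names no such check. In Safety assessment the only skin event named is at the ear, while the electrodes are on the limbs. That list is introduced as examples, so it does not show that reactions at the limb sites would go unrecorded.

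**3. Scale.** Input from Sample size: 404 randomised. The article gives no prevalence, so 1% to 5% is an assumption for illustration.
- 404 × 0.01 = 4.04, about 4 patients
- 404 × 0.05 = 20.2, about 20 patients

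**4. Sample size.** Inputs from Sample size: 70% against 85%, two-sided α = 0.05, power 90%, dropout 20%. With pooled variance under the null and no continuity correction:

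n = [1.960 × √(2 × 0.775 × 0.225) + 1.282 × √(0.70 × 0.30 + 0.85 × 0.15)]² / 0.15²

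= [1.960 × 0.5906 + 1.282 × 0.5809]² / 0.0225 ≈ 160.8, so 161 per group.

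Then 161 / 0.80 = 201.25, so 202 per group and 404 in total. The stated figures reproduce. No input depends on the proposed exclusion, so the required number does not change.

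**5. Recruitment cost of the fix.** If the same assumed share of otherwise eligible candidates were turned away:
- at 1%: 404 / 0.99 = 408.1, so 409 candidates, 5 more
- at 5%: 404 / 0.95 = 425.3, so 426 candidates, 22 more

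**The case against.** **This is a condensed article.** Skin checks and device contraindications may be in the full protocol or the stimulator's instructions. That is fair, and it means that enrolment of such patients is not shown. It does not dispose of the point: the article presents the list as the trial's criteria, in enough detail to include electrode allergy, and the list as written admits these patients.

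**Other limits apply.** Amplitude cannot exceed 10 mA, so a patient with reduced sensation never receives more than the plan allows anyone. The general-health exclusion removes some patients with advanced neuropathy and some device carriers. All participants are supervised inpatients. These limits stand and make the exposure smaller. They do not replace tolerance as the stated protection, and the general-health exclusion works by severity of disease, so isolated sensory loss or a local skin lesion passes it.

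**Implanted devices.** A reader might infer that carriers of a pacemaker or neurostimulator are exposed to a known danger, particularly as palpitation is a predefined event. The article does not support this. It says nothing about the stimulator's effect on such devices, and it lists palpitation among general symptoms without linking it to them.

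**No bias.** A reader might also infer that misapplied intensity distorts the result. It does not follow. Both arms use the same intensity rule, and allocation is random at 1:1, so affected patients are expected to fall evenly.

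**Conclusion.** The point holds as a limited safety and eligibility gap. The plan relies on felt tolerance to prevent pain and skin injury, yet it admits patients with reduced sensation at an electrode site, for whom that limit is unreliable. It also admits patients with broken skin there, against its own stated aim.

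The number affected is unknown; 4 to 20 of 404 rests entirely on the assumed 1% to 5% and takes no account of those whom the general-health exclusion would remove. The age range to 80 and the inpatient setting make such patients plausible, but the article does not establish that any will be enrolled. Sample size, power, type I error and the comparison between arms are unaffected. It would go too far to say that the safeguard fails for every group in the table: that argument fits sensory loss alone.

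**What to change.** Add one exclusion: sensory loss, or broken or infected skin, at any active or sham electrode site. Check it at the eligibility screen before randomisation. The check must cover the active and the sham sites in every candidate, because the arm is not yet known.

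For implanted electronic devices, reconcile the eligibility list with the stimulator's own labelled contraindications and state the result. The article gives no basis for going further.

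If the full protocol already contains these checks, stating them in the published criteria is enough.

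The cost is a line in the criteria, a brief examination at screening and the loss of a few candidates (5 to 22 extra to reach 404 under the assumed range). Because the check comes before randomisation and is the same for both arms, it introduces no imbalance. It slightly narrows the population to which the result applies.

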### Sample size

The sample size was calculated using a two-sample proportion test, with the following parameters: a two-sided significance level (*α*) of 0.05, a statistical power of 90% (*β* = 0.1), an expected qualified preparation rate of 70% for the sham TEAS group, and 85% for the active TEAS group. The calculated minimum evaluable sample size was 161 per group. Accounting for a 20% dropout rate, a total of 404 subjects were planned, with 202 subjects allocated to each group.

### Recruitment

This prospective study will recruit 404 adult participants scheduled for colonoscopy procedures across clinical indications at Zhejiang Provincial Hospital of Traditional Chinese Medicine. Enrollment is planned to commence in May 2025, with anticipated completion by June2026. To ensure protocol standardization, the study cohort was strictly limited to inpatients requiring scheduled colonoscopy under controlled clinical supervision. Recruitment methods mainly take place within hospitals, such as through clinician referrals and posters displayed in outpatient clinics. All recruitment activities will adhere to ethical standards, ensuring compliance with the principles of the Declaration of Helsinki (35).

### Randomization and blinding

This single-blinded trial implemented CONSORT-compliant randomization and blinding protocols (36), and subjects were assigned to the TEAS group and the sham-TEAS group in a 1:1 ratio. To ensure assessment objectivity, screening and outcome assessors remained blinded to treatment allocation status throughout the study period. All recordings were deidentified by removing all patient identifiers and temporal markers to eliminate assessment bias. The TEAS-administering acupuncturists maintained awareness of treatment allocation while remaining blinded to study outcomes. A computer-generated block randomization system with concealed allocation utilized numbered, sealed envelopes containing group assignments, secured by ward nurses until post-allocation unblinding. Primary endpoints were evaluated by two gastroenterologists independently conducted blinded assessments by reviewing endoscopic videos. A standardized operational protocol (fixed electrode stimulation duration) was implemented for double-blind control, while enabling dynamic adjustment of stimulation intensity based on individual tolerance thresholds. A blinding assessment will be conducted after colonoscopy completion and before unblinding, using a standardized questionnaire asking patients: “Which treatment do you think you received? (A. Active TEAS; B. Sham TEAS; C. Uncertain).” The success of blinding will be quantified by calculating the Bang Blinding Index.

